### 2.5. Recruitment

The present study aims to recruit 45 participants from Kyung Hee University Korean Medicine Hospital through advertisements on public transport or promotions in COVID-19 patient treatment facilities (e.g., National Medical Center) and related disease cohorts.

### 2.6. Blinding and Treatment Allocation

Due to the design characteristics of this clinical study without a control group, randomization, allocation concealment, and blinding will not be implemented. The investigator shall assign each patient a unique patient number at visit 0 (V. 0). To allocate patients to each herbal medicine group, the KM syndrome differentiation will be conducted by an internal medicine specialty Korean Medicine doctor (KMD) with a clinical experience of >10 years. According to the main sequelae symptoms after COVID-19, patients will be allocated to the fatigue or cognitive dysfunction group and then assigned to the appropriate herbal medicine intervention group based on each sub-syndrome differentiation pattern. The considerations for syndrome differentiation are shown in Table 2.

### 2.7. Intervention

Based on the syndrome differentiation diagnosis, three different herbal medications will be prescribed to each patient for up to 12 weeks. Among the patients with fatigue, the pattern/syndrome of lung-spleen qi deficiency group will be administered Bojungikgi-tang (CV1, Kracie Bojungikgitang Extract Fine Granule, Kolmar Pharma, Korea), and the syndrome of dual deficiency of qi and yin group will be administered Kyungok-go (CV2, Kyungbang Kyungokgo, KBPharm, Korea). The cognitive dysfunction group will be administered Cheonwangbosim-dan (CV3, Soonsimhwan, Hanpoong Pharm, Korea). Bojungikgi-tang (CV1) will be administered one sachet (3.75 g) twice a day before or in between meals. Kyungok-go (CV2) will be administered one sachet (20 g) twice a day in the morning and evening before or in between meals. Cheonwangbosim-dan (CV3) will be administered one sachet (one dose) once a day in between meals. The evaluation for the continuation of herbal medicine administration will be conducted at visits 2 and 3. If visual analog scale (VAS, 0–100) for fatigue or cognitive dysfunction at the current visit is improved by <50% of VAS at the previous visit, and the patients want to take herbal medicine, the same herbal medicine as previously prescribed will be re-administered for 4 weeks. For this evaluation, the symptom improvement rate at the current visit (VAS score of the current visit/VAS score of the previous visit (%)) and whether the patients want to continue the administration of herbal medicines will be investigated.

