### 2.8. Outcomes

#### 2.8.1. Primary Outcome

As the primary outcome, the treatment success rate after herbal medications for up to 12 weeks for fatigue and cognitive dysfunction in patients who have recovered from COVID-19 will be evaluated. VAS (0–100) for fatigue or cognitive dysfunction before (visit 1) and after administration of herbal medicines (visit 4) will be assessed. If VAS is >15 points, it is defined as treatment success. The frequency or ratio of treatment success patients will be presented, based on the fatigue and cognitive dysfunction groups, respectively.

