#### 2.8.2. Secondary Outcome

##### Medication Adherence

Medication adherence will be monitored by counting the number of returned and taken medications at each visit. In the case of the number of returned drugs and number of taken drugs being unmatched with the number of prescribed drugs, the reason for this shall be recorded in the case report form. Medication adherence is calculated as follows:$$Medication\;adherence\;\left(\%\right)=\frac{The\;number\;of\;taken\;drugs}{The\;number\;of\;prescribed\;drugs\;in\;the\;duration\;*}\times 100$$
* The number of prescribed drugs in the duration means the number of drugs should be taken from the time of initial administration to before the time of returning the untaken drugs.

The final medication adherence will be evaluated at 12 weeks after the initial administration (visit 4 or end point of medication), and the sum of the number of taken herbal medicines divided by the sum of the number of prescribed herbal medicines in the duration will be calculated and collected at visits 2, 3, and 4. Mean, standard deviation, median, minimum, and maximum value of the final medication adherences (%) for all study patients will be represented for each herbal medicine group, and multiple comparison analyses will be conducted among groups.

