## Figures and Tables

**Figure 1 healthcare-10-01839-f001:**
[figure not shown]
Flow diagram and schedule.

**Table 1 healthcare-10-01839-t001:** Schedule summary.

Visit	0	1	2	3	4	5	6	UV *
Week	−7	1	5	9	13	25	37	-
Visit Window	-	2	±7	±7	±7	±7	±7	-
Informed consent for the study	●							
Demographic information	●							
Participation in other clinical trials	●							
Medical history	●							
Confirmation of diagnosis of COVID-19 infection	●							
Medication history	●							
Vital signs	●	●	●	●	●	●	●	●
Electrocardiogram	●				●			●
Laboratory test	●				●			●
Blood collection for immune response and metabolite analysis	●				●	●	●	●
Pregnancy **	●							
Evaluation of fatigue or brain fog	●							
CIS	●		●	●	●	●	●	●
VAS (0–100) score for fatigue or brain fog	●		●	●	●	●	●	●
Inclusion/exclusion criteria	●							
KM syndrome differentiation		●						
Prescription of herbal medicine ***		●	○	○				
Drug adherence			●	●	●			●
Check for combination therapy			●	●	●	●	●	●
ChFQ		●	●	●	●	●	●	●
EQ-5D-5L		●	●	●	●	●	●	●
PSQI-K		●	●	●	●	●	●	●
K-MoCA		●	●	●	●	●	●	●
CFQ		●					●	●
BDI		●	●	●	●	●	●	●
Digit span test in K-WAIS (DF, DB, and DF-DB)		●			●	●	●	
K-BNT-15		●			●	●	●	
Adverse events check		●	●	●	●	●	●	●

●, check on visit; ○, if applicable * UV, unscheduled visit (), ** only fertile women, *** Evaluation for the continuation of herbal medicine administration at 5th and 9th weeks.

**Table 2 healthcare-10-01839-t002:** KM syndrome differentiation for allocation to treatment group.

	Fatigue		Cognitive Dysfunction
Code	CV1	CV2	CV3
Syndrome differentiation classification	Spleen-lung qi deficiency pattern	Dual deficiency of qi and yin pattern	Heart yin deficiency heat pattern
Symptom	Fatigue, appetite loss, cold sweat, shortness of breath, chest tightness, anxiety and others	Fatigue, dry cough and others	Forgetfulness, fever, insomnia, heart palpitation, stomatitis, tongue needles and others
Tongue diagnosis	Pale tongue, thin white fur	Dry mouth, dry tongue	Red tongue and low tongue coated
Pulse diagnosis	Vacuous, large, weak pulse/surging, large pulse	Fine pulse/vacuous, weak pulse	Fine, rapid pulse
Urine/feces	Difficult stool to pass/sloppy stool	Dry stool	Inhibited stool/sloppy stool

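### The improvement rate defined for the herb-renewal decision (section 2.7) is the share of symptom remaining, so comparing it with the stated 50% cut-off reverses who is re-treated

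*Protocol article*

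**What the plan says.** Section 2.7 sets up a response-guided course of at most 12 weeks, with a renewal decision at visits 2 and 3. The footnote to Table 1 repeats the timing: "Evaluation for the continuation of herbal medicine administration at 5th and 9th weeks".

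The decision sentence applies when the VAS for fatigue or cognitive dysfunction "is improved by <50% of VAS at the previous visit, and the patients want to take herbal medicine". In that case "the same herbal medicine as previously prescribed will be re-administered for 4 weeks".

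The sentence after it says what is to be recorded to make the decision: "For this evaluation, the symptom improvement rate at the current visit (VAS score of the current visit/VAS score of the previous visit", in percent, together with whether the patient wishes to go on. It repeats no threshold.

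On when the VAS is taken, section 2.8.1 says that the scores "before (visit 1) and after administration of herbal medicines (visit 4) will be assessed". In Table 1 the row "VAS (0–100) score for fatigue or brain fog" is marked at visits 0, 2, 3, 4, 5 and 6 and at unscheduled visits. It is not marked at visit 1.

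**The concern.** Two consecutive sentences describe the same decision with quantities that run in opposite directions. The first speaks of improvement. The second gives the name of an improvement rate to current score divided by previous score, which gets larger as the patient does worse. Someone who computes the rate as defined and holds it against the cut-off in the sentence before will renew and stop the wrong patients, if the words are what was meant.

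This is a dosing rule. It settles whether a willing patient has had 4, 8 or 12 weeks of herb by visit 4, where the primary outcome is read. Section 2.3 intends the results to inform the size of later confirmatory trials, so the regimen behind the success rate should be reproducible from the text.

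A second gap affects the same calculation. At visit 2 the previous visit is visit 1, and Table 1 schedules no VAS there.

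**Working it through.** There is no stated figure to reproduce. The check compares the two definitions.

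**Inputs.** Cut-off of 50% and worded direction: section 2.7. Ratio of current to previous VAS: section 2.7. Renewals of 4 weeks at visits 2 and 3, and the 12-week maximum: section 2.7. VAS schedule: Table 1 and section 2.8.1. Assumption: a higher VAS means worse symptoms, as is usual for a symptom scale.

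**Formulas.** Let P be the previous VAS and C the current VAS.

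- Improvement: F = (P − C)/P × 100. The words renew if F < 50.
- Ratio as defined: R = C/P × 100 = 100 − F. With the same cut-off, the formula renews if R < 50, that is, if F > 50.

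**Numbers, for an assumed previous VAS of 80 in a patient who wishes to continue:**

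| Current VAS | F (%) | R (%) | Words | Ratio against <50% |
|---|---|---|---|---|
| 0 | 100 | 0 | stop | renew |
| 20 | 75 | 25 | stop | renew |
| 40 | 50 | 50 | stop | stop |
| 60 | 25 | 75 | renew | stop |
| 80 | 0 | 100 | renew | stop |
| 90 | −12.5 | 112.5 | renew | stop |

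Because R = 100 − F, the two decisions coincide only at F = 50, where neither renews.

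**Exposure for one patient.** The first supply is 12 − 2 × 4 = 4 weeks, which agrees with visits 1 and 2 at weeks 1 and 5. Two constructed courses over the pre-treatment, visit 2 and visit 3 scores show the range:

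- 80, 48, 28.8: F = 40 and 40; R = 60 and 60. Words: 4 + 4 + 4 = 12 weeks. Ratio: 4 weeks.
- 80, 30, 12: F = 62.5 and 60; R = 37.5 and 40. Words: 4 weeks. Ratio: 4 + 4 + 4 = 12 weeks.

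The two readings can therefore differ by 12 − 4 = 8 weeks for one patient. These courses are illustrations, not expected trajectories.

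**Denominator.** At visit 3 the previous VAS is that of visit 2, which Table 1 schedules. At visit 2 it would be that of visit 1, which section 2.8.1 presupposes and Table 1 does not schedule. The only pre-treatment VAS in Table 1 is at visit 0.

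**With the rate corrected** to (P − C)/P × 100 and P = 80: C = 60 gives 25%, renew; C = 40 gives 50%, stop; C = 20 gives 75%, stop. This matches the words.

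**The case against.** The strongest reply is that section 2.7 contains only one decision sentence, and it is worded correctly. The sentence with the ratio states no threshold and no action. It lists what will be recorded, and staff could take the complement of the ratio and apply the worded rule. The worded rule also makes clinical sense, since it continues treatment while relief is insufficient, and it fits a course of up to 12 weeks. All of this stands, and it is why the words are probably what was intended. It does not remove the error. The ratio carries the name of an improvement rate, it is tied to this evaluation, and no other cut-off is given. If it is only raw data, its label is wrong. If the decision sentence was meant to say improved to below 50%, then the words are wrong instead.

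A reader might infer that the trial will deliver two opposite regimens, or a mixture of them. The document does not show that. Section 2.5 names one recruiting hospital, and nothing indicates that investigators would apply different rules. Nor does counting the score pairs on which the readings disagree measure the problem: such a count only restates R = 100 − F and says nothing about patients.

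A reader might also see a conflict between the 12-week course in the abstract and objectives and the shorter courses that the rule allows. That is shorthand for the maximum. Section 2.8.1 refers to "the treatment success rate after herbal medications for up to 12 weeks for fatigue and cognitive dysfunction", and the adherence section allows for an earlier end: "The final medication adherence will be evaluated at 12 weeks after the initial administration (visit 4 or end point of medication". No change is needed there.

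Finally, the ratio is not an endpoint. Success is read from the VAS at visit 4 whatever the weeks of herb, in an uncontrolled preliminary study of 45 patients. This limits the consequence, but the rule still sets the exposure that precedes that reading.

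**Conclusion.** The point holds as an error of definition in a dosing rule, and it should be fixed. The quantity named as improvement is its complement. Used with the stated cut-off, it reverses the renewal decision at every value except a fall of exactly 50%, and for a single patient it can change exposure by up to 8 of 12 weeks. The reversal rests on two assumptions: that the cut-off in the decision sentence carries over to the defined rate, and that a higher VAS is worse. The mislabelling needs neither, since an unchanged score reads as 100% on any scale direction.

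It would go too far to conclude that the success rate is biased. The document gives no basis for how many patients would be affected, or for the size or direction of any shift.

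The missing visit 1 VAS is a separate, smaller inconsistency. It matters here because the visit 2 decision cannot be computed literally from the scheduled measurements.

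**What to change.** In section 2.7, define the improvement rate as (previous VAS − current VAS)/previous VAS × 100, and renew for 4 weeks if it is below 50% and the patient wishes to continue. Equivalently, keep the ratio, call it the share remaining, and renew if it is above 50%. Both versions stop at exactly 50%, as the words do.

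Name the visit 0 VAS as the denominator for the visit 2 decision, in agreement with Table 1.

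The sponsor should confirm that the worded rule is the intended one. The cost is one corrected formula and one named baseline score, with no added patient, visit or measurement.

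### Section 2.7 defines the symptom improvement rate as the share of VAS remaining, against its own continuation rule, and Table 1 does not schedule the visit 1 VAS that the text relies on

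*Protocol article*

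**What the plan says.** Four statements in the protocol article bear on this point.

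- **Timing (section 2.7).** "The evaluation for the continuation of herbal medicine administration will be conducted at visits 2 and 3".
- **Rule (section 2.7).** The test is whether the patient's symptom VAS "is improved by <50% of VAS at the previous visit". If it is met, and the patient also wishes to go on, "the same herbal medicine as previously prescribed will be re-administered for 4 weeks".
- **Recorded quantity (section 2.7, next sentence).** "For this evaluation, the symptom improvement rate at the current visit" is collected, together with the patient's wish to continue. The rate is defined in brackets as "VAS score of the current visit/VAS score of the previous visit", in per cent. No separate cut-off is attached to it.
- **VAS schedule.** In Table 1 the row "VAS (0–100) score for fatigue or brain fog" is marked at visit 0, blank at visit 1, and marked at visits 2 to 6 and at unscheduled visits. Section 2.8.1 places the pre-treatment VAS for the primary outcome at visit 1 and the post-treatment VAS at visit 4.

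**The concern.** The bracketed definition contains no subtraction. A quantity that scores an unchanged patient at 100% does not measure improvement, whichever way the scale runs, so the definition contradicts the sentence before it. The only threshold in the section is 50%, and the ratio is the only derived number the section says is collected for the decision. A case report form or worksheet built from the bracket could therefore set the 50% limit against the wrong quantity. Nothing on the page would flag this, because a ratio in per cent looks like a plausible rate.

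The second problem is the reference value. At visit 3 the previous visit is visit 2, where VAS is scheduled. At visit 2 the previous visit is visit 1, where Table 1 schedules none. Section 2.8.1 agrees with the literal reading of section 2.7 in using visit 1, so this is a conflict between text and schedule.

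At stake is whether a willing patient receives another 4-week course, and hence how much treatment precedes the visit 4 primary outcome.

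**Working it through.** The plan gives no figure to reproduce here, so the check is algebraic, followed by a comparison of text and table.

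**Inputs.** Section 2.7 supplies the prose rule (improvement below 50%) and the printed rate (current VAS divided by previous VAS). Table 1 supplies the visits with a VAS. The VAS values below are illustrations. I assume that higher VAS is worse; the article does not state the direction, but it is the natural reading for a fatigue or cognitive-dysfunction scale.

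**Step 1: relate the two quantities.** Let R = 100 × current/previous (the printed rate) and I = 100 × (previous − current)/previous (improvement). Then I = 100 − R.

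**Step 2: apply the threshold to each.** Under the prose rule a willing patient continues if I < 50, which is the same as R > 50. If the 50% limit is instead read against the printed rate, the patient continues if R < 50. These conditions are opposite except at R = 50, where neither is met and both say stop.

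**Step 3: put numbers in** (willing patients; stop means not re-administered).

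| VAS, previous to current | Printed rate R | Improvement I | Prose rule | 50% limit applied to R |
|---|---|---|---|---|
| 80 to 80 | 80/80 = 100% | 0% | continue | stop |
| 80 to 70 | 70/80 = 87.5% | 12.5% | continue | stop |
| 80 to 40 | 40/80 = 50% | 50% | stop | stop |
| 80 to 20 | 20/80 = 25% | 75% | stop | continue |
| 80 to 0 | 0/80 = 0% | 100% | stop | continue |
| 60 to 75 (worse) | 75/60 = 125% | −25% | continue | stop |

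**Step 4: check the reference visit.**

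| Decision | Previous visit | VAS scheduled there in Table 1? |
|---|---|---|
| Visit 2 | Visit 1 | No |
| Visit 3 | Visit 2 | Yes |

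The VAS row in Table 1 has one cell for each of its eight visit columns, so the blank at visit 1 is not a reading fault. The only scheduled VAS before treatment is at visit 0, and neither section 2.7 nor section 2.8.1 names it.

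**The case against.** The strongest reply is that the rule works without the bracket. The prose sentence is complete and correct, the ratio carries no cut-off of its own, and since R = 100 − I it holds all the information the rule needs. On that view this is a mislabelled data item. The reversal also needs someone to move the prose threshold onto the ratio, a step the document does not prescribe. Continuation depends on the patient's wish as well, no planned test or reported outcome uses the ratio, and this is an uncontrolled preliminary study of 45 patients. All of that stands. It limits the consequence but does not make the definition right.

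Two stronger readings are tempting, and the documents support neither.

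- *The protocol's continuation rule is reversed, so the wrong patients will be treated.* The operative sentence points the right way, and staff who follow it decide correctly. The reversal is conditional on misapplying the threshold.
- *The visit 2 decision has no pre-treatment VAS, or leaves sites free to pick any reference.* Section 2.7 refers to the previous visit without naming visit 1, but the visit order implies it, and section 2.8.1 names visit 1 outright. A visit 0 value is also scheduled. The text is consistent with itself; what fails is its match with Table 1.

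**Conclusion.** Wrong as written, and minor. The bracketed rate in section 2.7 is the share of VAS remaining and contradicts the rule it is meant to serve. Calling it the share of symptom remaining assumes that higher VAS is worse. That it is not an improvement rate needs no such assumption, because no change gives 100%. If the 50% limit were applied to it, decisions for willing patients would reverse everywhere except at an exact halving.

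The reference visit is a separate text-versus-table conflict. It affects the visit 2 decision and the pre-treatment value in section 2.8.1, but not the visit 3 decision.

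The harm is conditional on how the form is built and read. The document gives no basis for estimating how many patients would be affected.

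**What to change.** 1. In section 2.7, define improvement rate (%) = 100 × (previous VAS − current VAS)/previous VAS, and re-administer for 4 weeks if it is below 50% and the patient wishes to continue. Equivalently, keep the ratio, rename it VAS remaining (%), and re-administer if it is above 50%. Either way the cost is one corrected expression.
2. Settle the pre-treatment VAS in one of two ways.
   - Mark VAS at visit 1 in Table 1. This agrees with sections 2.7 and 2.8.1 as they stand and costs one extra self-rating at a visit that already takes place.
   - Name visit 0 as the pre-treatment VAS in section 2.7 (for the visit 2 decision) and in section 2.8.1. This needs no new measurement, but both sections must change. Editing section 2.7 alone would leave the continuation rule and the primary outcome on different baselines.

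The visit 3 decision keeps visit 2 as its reference.

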### 2.8. Outcomes

#### 2.8.1. Primary Outcome

As the primary outcome, the treatment success rate after herbal medications for up to 12 weeks for fatigue and cognitive dysfunction in patients who have recovered from COVID-19 will be evaluated. VAS (0–100) for fatigue or cognitive dysfunction before (visit 1) and after administration of herbal medicines (visit 4) will be assessed. If VAS is >15 points, it is defined as treatment success. The frequency or ratio of treatment success patients will be presented, based on the fatigue and cognitive dysfunction groups, respectively.

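### The primary outcome and the visit 2 re-supply decision both need a VAS at visit 1, but Table 1 schedules none there

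*Protocol article*

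**What the plan says.** Section 2.8.1 makes the treatment success rate the primary outcome. It states that the VAS "before (visit 1) and after administration of herbal medicines (visit 4) will be assessed", and sets the criterion: "If VAS is >15 points, it is defined as treatment success". Because two visits are named, the 15 points are evidently meant as the change between them, although the sentence does not use the word.

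Section 2.7 uses the same scale to decide who receives more medicine: "The evaluation for the continuation of herbal medicine administration will be conducted at visits 2 and 3". The same medicine is given for another 4 weeks if the patient wants it and the VAS "at the current visit is improved by <50% of VAS at the previous visit".

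Table 1 has a row labelled "VAS (0–100) score for fatigue or brain fog". It is marked at visits 0, 2, 3, 4, 5, 6 and the unscheduled visit, and the visit 1 cell is empty. Syndrome differentiation and the first prescription take place at visit 1, so visit 0 is before treatment and is the only pre-treatment visit with a VAS. Section 2.6 describes the trial as "this clinical study without a control group".

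**The concern.** The text and the schedule disagree on when the baseline of the primary outcome is measured. Site staff work from the schedule. If they follow it, no visit 1 VAS exists, and neither the success criterion in Section 2.8.1 nor the visit 2 comparison in Section 2.7 can be applied as written.

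The obvious stopgap is the visit 0 value, but it answers a slightly different question. The fall from visit 0 to visit 4 includes whatever happened before the first dose, and without a comparison group nothing subtracts that part. Improvement before treatment would raise the success rate and worsening would lower it.

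The success rate is the primary objective in Section 2.1, and Section 2.3 says that the results will be used to size confirmatory trials. An ambiguity in its baseline would therefore carry forward.

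**Working it through.** No figure in the plan has to be reproduced here. The check sets the visits that the text needs beside the visits that Table 1 schedules.

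| Use of the VAS | Source | Visits needed | Marked in Table 1? |
|---|---|---|---|
| Primary outcome | Section 2.8.1 | 1 and 4 | 1 no, 4 yes |
| Re-supply at visit 2 | Section 2.7 | 1 and 2 | 1 no, 2 yes |
| Re-supply at visit 3 | Section 2.7 | 2 and 3 | both yes |

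Only visit 1 is needed and not scheduled. It affects the primary outcome and the first re-supply decision. The visit 3 decision and the visit 4 value are covered.

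**Is the blank cell a text-extraction fault?** The header has eight visit columns (0 to 6 and unscheduled), and the VAS row has all eight cells. Neighbouring rows line up with the header: vital signs are marked in every column, and syndrome differentiation at visit 1 only. Eight scales (ChFQ, EQ-5D-5L, PSQI-K, K-MoCA, CFQ, BDI, digit span, K-BNT-15) are blank at visit 0 and marked at visit 1. The CIS row is marked at visit 0 and blank at visit 1, as the VAS row is. The blank is in the table itself.

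**Does the wording of the re-supply rule matter?** Section 2.7 speaks of improvement, but prints the rate as the current score divided by the previous one. On either reading the earlier score is required, so the visit 2 decision needs a visit 1 value.

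**What does using visit 0 do?** Write V0, V1 and V4 for the scores at visits 0, 1 and 4. Then

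V0 − V4 = (V0 − V1) + (V1 − V4).

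The last term is the change over the treatment period that Section 2.8.1 describes. The first is pre-treatment change, which the visit 0 baseline adds to it. An invented case shows the mechanism, not its size: with scores of 60, 50 and 40, the fall is 60 − 40 = 20 from visit 0, above 15, but 50 − 40 = 10 from visit 1, not above 15.

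**How long is the gap?** The Week row of Table 1 prints −7 for visit 0 and 1 for visit 1. If −7 means days, the gap is about 1 week. If it means weeks, as the row label says, it is 1 − (−7) = 8 weeks. The row below gives a window of ±7 for visits at weeks 5, 9 and 13. Those visits are 4 weeks apart, so that window can only be in days, which makes days the likelier unit for −7 as well.

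**The case against.** The strongest reply is that Table 1 is coherent by itself and the slip is in Section 2.8.1. No efficacy scale is marked at both visit 0 and visit 1. VAS and CIS have their one pre-treatment mark at visit 0, and the other eight scales have theirs at visit 1. Laboratory tests, electrocardiogram and research blood are also taken before treatment only at visit 0, and Section 2.9 evaluates laboratory changes from baseline. On this view visit 0 is the intended baseline and the visit number in Section 2.8.1 is loose wording.

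That may be so, and it is why naming visit 0 is offered as an alternative correction. It does not remove the conflict. Section 2.8.1 names visit 1 outright, the rule in Section 2.7 points to it independently, and no sentence carries the visit 0 score forward. A separate analysis plan could choose visit 0, but it could not recover a visit 1 score that was never taken.

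Three stronger readings are tempting, and the document supports none of them.

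- A reader might infer that baseline lies 8 weeks before treatment. The ±7 window row speaks against this. An 8-week gap would also leave the screening laboratory and pregnancy tests two months old at the first dose, with no repeat scheduled.
- A reader might infer a substantial inflation of the success rate. The article gives no VAS mean, standard deviation or pre-treatment trend, so any figure would come from assumed inputs.
- A reader might infer that staff are free to choose between two baselines. If Table 1 is followed, only visit 0 exists. If a visit 1 score is also taken, Section 2.8.1 says to use it.

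**Conclusion.** Wrong as written. The schedule does not collect a value on which the primary outcome and the visit 2 re-supply decision both rest. This follows from the text and the table alone, with two modest readings: the 15 points in Section 2.8.1 are a change between the two named visits, and the visit preceding visit 2 is visit 1.

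The effect on the success rate cannot be computed from the article. It depends on how much the VAS changes between visit 0 and the first dose, over a gap that is probably about 1 week. If there is no average drift, the expected rate may shift little, although individual patients near the threshold could still be classified differently. The point is more than clerical because the study is uncontrolled: a baseline taken before the first dose at visit 1 keeps earlier change out of the result, and no later analysis can do that if the score is missing.

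**What to change.** Preferred: mark the VAS at visit 1 in Table 1, taken before the first dose. State in Sections 2.7 and 2.8.1 that this one value serves the success criterion and the visit 2 continuation decision. The visit 3 decision stays against visit 2, as now.

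Alternative: if visit 0 is the intended baseline, name it in both sections, and label the −7 in Table 1 as days or weeks. This settles the conflict, but leaves any change before the first dose inside the success rate.

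The preferred change costs one short scale at a visit that already carries eight others. The alternative costs only wording.

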### 2.3. Sample Size

The current study is a phase 2 preliminary clinical study, thus we will recruit 45 patients without sample size calculations. Fifteen patients will be assigned to each of the three intervention groups. The results from this study will be used to calculate the sample size for further confirmatory clinical trials.

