### 2.4. Participants

#### 2.4.1. Inclusion Criteria

The inclusion criteria are as follows:Those aged >19 years and have been diagnosed with COVID-19 and recovered. To confirm the COVID-19 diagnosis and recovery, medical history will be examined by reviewing the submitted medical records about the diagnosis, hospitalization, and certificate of SARS-CoV-2 negative or conduct COVID-19 antibody test using the COVID-19 IgM/IgG Plus Test kit (Sugentech, Inc., Daejeon, Korea) approved by the Korean Ministry of Food and Drug Safety. If submission of medical records is possible, the antibody test can be skipped.Those who are continuously complaining of fatigue or cognitive dysfunction for >4 weeks that they did not experience before their COVID-19 diagnosis.Those who scored a total of >76 points on the Checklist Individual Strength (CIS).Participants do not have any problems with overall cognitive function and must be capable of providing written informed consent to participate in the study.

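### The primary success rule is written as a VAS level above 15 points although a change from baseline appears intended; read literally, it counts unimproved patients as successes and the most improved as failures

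*Protocol article*

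**What the plan says.** Section 2.8.1 of the protocol article makes the treatment success rate the primary outcome. It first fixes the measurements: "VAS (0–100) for fatigue or cognitive dysfunction before (visit 1) and after administration of herbal medicines (visit 4) will be assessed". It then gives the rule: "If VAS is >15 points, it is defined as treatment success". The rate is to be reported by symptom group: "The frequency or ratio of treatment success patients will be presented, based on the fatigue and cognitive dysfunction groups, respectively".

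No other section defines success. Section 2.1 names the treatment success rate as the primary objective without saying how it is scored, and section 2.12 does not mention it. VAS appears in one other rule, the continuation check in section 2.7, which asks whether the score "is improved by <50% of VAS at the previous visit" and works from the ratio "VAS score of the current visit/VAS score of the previous visit". That rule decides whether medication is re-prescribed and does not bear on the endpoint.

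Table 1 marks VAS at visits 0, 2, 3, 4, 5 and 6 and at unscheduled visits. It has no mark at visit 1.

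**The concern.** As a sentence, the success rule compares a single score with 15. It does not say that two scores are subtracted, which is taken from which, or at which visit the comparison is made. On a scale of symptom severity, a score above 15 means that symptoms are still present, which is the opposite of success.

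This is the trial's only primary outcome, and there is no control group against which an odd success rate would stand out. The result is also meant to be carried forward: "The results from this study will be used to calculate the sample size for further confirmatory clinical trials". A success rate from the literal rule would be unusable for that purpose. One from an unstated rule would depend on how the analyst filled the gap, possibly after seeing the data.

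**Working it through.** The plan gives no expected success rate or power ("thus we will recruit 45 patients without sample size calculations"), so there is no figure of its own to reproduce. The check compares two rules:

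- Literal rule: success if VAS at visit 4 > 15.
- Change rule: success if baseline VAS − VAS at visit 4 > 15.

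**Direction of the scale.** The anchors are not given. The VAS is labelled as a score for fatigue or cognitive dysfunction, and section 2.7 expresses improvement as a share of the previous score. Both point to lower being better.

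**Single patients** (the two rules applied to example scores):

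| Baseline → visit 4 | Fall | Literal rule | Change rule |
|---|---|---|---|
| 70 → 85 | −15 | success | failure |
| 70 → 70 | 0 | success | failure |
| 70 → 60 | 10 | success | failure |
| 70 → 40 | 30 | success | success |
| 70 → 15 | 55 | failure | success |
| 70 → 5 | 65 | failure | success |

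The rules agree only for patients who improve by more than 15 points yet remain above 15. They disagree for patients without improvement and for those with the most.

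**Group rates, by hand.** The means, SDs and correlation here are assumptions, because the documents give none. With visit 4 VAS normal with mean m and SD s, the literal rate is 1 − Φ((15 − m)/s). For s = 20:

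- m = 60: 1 − Φ(−2.25) = 0.988
- m = 40: 1 − Φ(−1.25) = 0.894
- m = 30: 1 − Φ(−0.75) = 0.773

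For the change rule with mean fall d, equal SDs s and correlation r, the SD of the fall is s√(2(1 − r)). With s = 20 and r = 0.5 this is 20, and the success rate is 1 − Φ((15 − d)/20). That is 1 − Φ(0.75) = 0.227 at d = 0 and 1 − Φ(−0.75) = 0.773 at d = 30.

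**Group rates, by simulation.** Scores were clipped to 0–100, because the normal model runs off the scale. The baseline mean was 50, 60 or 70, the SD 15 or 20, and the correlation 0.5. Ranges across these six settings:

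| Mean fall | Literal rule | Change rule |
|---|---|---|
| 0 | 96.0–100.0% | 15.5–22.6% |
| 15 | 84.2–99.6% | 49.1–50.0% |
| 30 | 59.9–95.2% | 75.9–84.1% |
| 50 | 15.8–63.1% | 92.9–99.0% |

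The percentages depend on the assumptions. The direction does not: any downward shift in visit 4 scores can only lower the share above 15.

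**Baseline visit.** Section 2.8.1 takes the pre-treatment VAS at visit 1. Table 1 schedules it at visit 0 and not at visit 1. A change score needs one named baseline, so these two places conflict on an input to the corrected rule.

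**The case against.** The strongest reply is that this is a dropped word. A before-and-after pair followed by a threshold for success reads naturally as a change, and few analysts would count an unchanged patient as a success. Much of this stands: a reduction is the likely intent, and both visits are named. A reader might infer that the trial's answer will in fact come out inverted, but the documents support only that it would if the sentence were followed as written.

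The reply does not remove the defect. Supplying the word for change still leaves the direction and the baseline visit open. Nor is this a detail left out in condensing a protocol for a journal: the article states the rule, and states it wrongly.

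The opposite overreach is to treat a fall of more than 15 points as the established rule. The article never says it, so the sponsor has to confirm it.

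A reader might also argue that entry rests on the fatigue checklist alone ("Those who scored a total of >76 points on the Checklist Individual Strength (CIS"), so that patients could enter with a VAS too low to fall by more than 15. There is indeed no minimum VAS, but section 2.4.1 also requires more than 4 weeks of fatigue or cognitive complaints that were absent before COVID-19. Nothing suggests that such patients would score 15 or less on their main symptom. An entry threshold just above 15 would help little, since a patient entering at 16 would have to fall below 1.

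Finally, a reader might want the share worsening by more than 15 points as a benchmark for the uncontrolled success rate. Patients enter because they are symptomatic, so regression to the mean and natural recovery push scores down. That share would understate the success expected without a drug effect.

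**Conclusion.** The rule is wrong as written and must be corrected. Applied at visit 4 with lower scores better, it counts unchanged and worsened patients above 15 as successes and patients who reach 15 or below as failures. Its rate therefore moves against benefit.

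Two inferences support this. The direction of the scale comes from its label and from section 2.7; if higher were better, a level above 15 would still not measure improvement. The intention to use a reduction comes from the before-and-after sentence.

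The percentages illustrate the size of the error under assumed means, SDs and correlation, and do not predict this trial's results. The 16–23% success with no mean change under the change rule is a feature of dichotomising a noisy difference and no part of the error found here.

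**What to change.** Replace the sentence in section 2.8.1 with a change rule: treatment success is baseline VAS minus visit 4 VAS greater than 15 points, on the VAS of the patient's main symptom (fatigue or cognitive dysfunction). The sponsor should confirm that an absolute reduction is meant, and state the VAS anchors so that the direction is explicit.

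In the same edit, name the baseline visit and bring section 2.8.1 and Table 1 into line. If visit 0 is the baseline, the text in section 2.8.1 changes. If visit 1 is, Table 1 needs a VAS assessment there.

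The cost is one sentence plus one reconciliation. Eligibility and sample size do not change. No new data are needed if the baseline is the visit 0 score already scheduled; otherwise one short rating is added at visit 1. The change should be dated and made before outcome data are analysed.
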